### Participants and Recruitment

Participants were first-year undergraduate students enrolled at Kansas State University during the Fall 2025 semester. Eligibility criteria included: (1) age ≥ 18 years at enrollment; (2) enrollment in their first college term immediately following high school graduation; (3) ownership of a compatible smartphone to complete daily surveys and synchronize wearable data; (4) residence in on-campus housing; and (5) absence of mobility impairments that would substantially alter gait patterns, as many research-grade accelerometer- and consumer wearable-based PA algorithms are validated in ambulatory populations with typical gait patterns. Students participating in varsity or club athletics were excluded to reduce heterogeneity in structured PA exposure and related scheduling demands that may differ systematically from those of the general student population.

Recruitment targeted the incoming freshman class (approximately 4,000 students) prior to and during the start of the Fall 2025 semester using a multi-pronged outreach strategy. Specifically, recruitment included: (1) printed handouts containing a QR code linking to an online eligibility screener, distributed in onboarding packets during in-person orientation visits in June 2025; (2) email announcements sent to the incoming class in July 2025; (3) advertisements posted on the Canvas page for incoming School of Health Sciences students during Summer 2025; (4) in-person tabling at a university-wide orientation event during move-in week; (5) in-person announcements and tabling at School of Health Sciences orientation events; and (6) advertisements posted on Psychology 101 course shells. Interested students completed an online screening survey to determine eligibility and were contacted promptly if eligible. Follow-up correspondence occurred in early August to schedule baseline laboratory visits.

### Sample Size Calculation

The present study was powered based on the intensive burst (daily diary) component rather than the monthly panel surveys, as primary hypotheses focused on within-person daily associations between 24-hour movement behaviors and depressive symptoms. Sample size considerations for intensive longitudinal designs are influenced by the number of participants, number of repeated observations per participant, and expected within-person effect sizes.^48,49^ Daily diary studies examining PA and affect, including negative affect items that reflect depressive symptoms, have typically observed small within-person effects.^50–53^ Assuming a small effect size (d = 0.20) and approximately 30–35 daily observations per participant across the five bursts, simulation-based estimates suggested that approximately 107 participants would provide 80% power to detect within-person effects.^54,55^ Allowing for up to 30% attrition across the semester, we aimed to recruit 139 participants.

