### Baseline Cohort Characteristics

A total of 144 students were enrolled in the study and completed baseline assessments. Baseline characteristics are presented in Table 2. Participants were approximately 18 years of age and slightly more likely to identify as female (54.9%) than male. The sample was predominantly White (78.5%), with 16.7% identifying as first-generation college students. Students were enrolled across multiple academic colleges within the university, most commonly Health and Human Sciences (29.9%), Engineering (27.8%), and Arts and Sciences (20.8%). At baseline, 80.6% of participants reported no prior mental health diagnosis, 16.0% reported a current diagnosis, and 2.1% reported a previous diagnosis that was not current. All participants provided informed consent prior to participation. The study protocol was approved by the Kansas State University Institutional Review Board (IRB #12780).

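### The recruitment target of 139 is 107 × 1.30; keeping about 107 participants after 30% attrition needs 153, so 139 covers about 23% attrition, not 30%

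*Protocol article*

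**What the plan says.** The Sample Size Calculation section bases the study's size on the daily diary component, because the primary hypotheses concern within-person daily associations. It assumes a small effect (d = 0.20) and "approximately 30–35 daily observations per participant across the five bursts". On that basis, "simulation-based estimates suggested that approximately 107 participants would provide 80% power to detect within-person effects". The next sentence gives the recruitment target: "Allowing for up to 30% attrition across the semester, we aimed to recruit 139 participants".

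Baseline Cohort Characteristics gives the number actually obtained: "A total of 144 students were enrolled in the study and completed baseline assessments".

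The article does not state the inflation formula, the significance level or whether the test is one- or two-sided. It gives no other route from 107 to 139.

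**The concern.** The two sentences give a base (about 107), an attrition allowance (up to 30%) and a result (139), and the three do not agree. An allowance for attrition is meant to leave the required number after the loss. The loss applies to everyone recruited, so the required number must be divided by the retained fraction. Multiplying by one plus the attrition rate always gives too few, and the gap widens as the rate rises. At 30% it is no longer negligible.

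What is at stake is how the eventual retention figure will be read. This is the only sample-size justification in the article, and readers will compare realised attrition with the 30% ceiling. If attrition falls between 25.7% and 30%, the article would suggest that the planned number had been kept when it had not.

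**Working it through.** **Inputs.** All are in Sample Size Calculation except the last:
- participants required: about 107, for 80% power
- attrition allowance: up to 30%
- recruitment target: 139
- enrolled: 144 (Baseline Cohort Characteristics)

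The base of 107 comes from a cited simulation whose settings are not given. It is taken as stated.

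**1. Reproducing 139.** Multiplying: 107 × (1 + 0.30) = 139.1, which rounds to 139. Dividing: 107/(1 − 0.30) = 152.86, which rounds up to 153. Only the first gives the stated figure.

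**2. Number needed.** 153 recruits leave 153 × 0.70 = 107.1. That is 14 more than the target of 139 and 9 more than the 144 enrolled.

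**3. What 139 and 144 give.**

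| Recruited | Left at 30% attrition | Highest attrition that leaves 107 |
|---|---|---|
| 139 | 139 × 0.70 = 97.3 | 1 − 107/139 = 23.0% |
| 144 | 144 × 0.70 = 100.8 | 1 − 107/144 = 25.7% |
| 153 | 153 × 0.70 = 107.1 | 1 − 107/153 = 30.1% |

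**4. Sensitivity to the base.** The article says approximately 107. A base of 105 needs 105/0.70 = 150 recruits, and a base of 109 needs 109/0.70 = 155.7, so 156. No base in that range lets 139 or 144 cover 30%.

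**5. Approximate power at 30% attrition.** This step needs assumptions that the article does not supply: alpha 0.05; a noncentrality that scales with the square root of the number of participants, anchored at 80% for 107; and no diary data from anyone who drops out. For a two-sided test, power = Φ(2.802 × √(n/107) − 1.960), where 2.802 = 1.960 + 0.842.
- 139 recruited, n = 97.3: 76.2%
- 144 enrolled, n = 100.8: 77.6%

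A one-sided test at 0.05 gives 76.6% and 77.9%.

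**6. If dropouts contribute some diary days.** Suppose, for illustration, that a dropout counts in proportion to the days completed out of 35. Then 107 person-equivalents are reached at 30% attrition if dropouts supply the following share on average:
- 144 enrolled: (107 − 100.8)/(144 × 0.30) = 6.2/43.2 = 14%, about 5 days
- 139 recruited: (107 − 97.3)/(139 × 0.30) = 9.7/41.7 = 23%, about 8 days

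With a 20% share, the formula in step 5 gives about 79.5% power for 139 and about 81% for 144.

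**The case against.** The strongest reply is that the slip has little consequence. The 30% is a ceiling, and the cohort that exists is 144, not 139. That cohort keeps 107 for any attrition up to 25.7%. The primary models are multilevel (Data Analyses, Aim 1), and Study Protocol codes the burst days missed by late enrollees as missing and does not remove the person. Someone who leaves mid-semester may therefore still contribute completed diary days. On the proportional count above, less than one 7-day burst per dropout would restore 107 person-equivalents among the 144.

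Much of this stands, and it limits the size of the point. It does not rescue the sentence. The section inflates a count of participants and does not invoke partial data. A target said to allow for attrition up to 30% has to hold at 30%. The observation count offers no evident slack either: 30 to 35 diaries out of a maximum of 35 (five 7-day bursts) is 86% to 100% completion.

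A reader might go further and infer that the study fails to reach 80% power. The article does not support that. It attaches 80% power to about 107 participants and mentions attrition in a separate sentence. It reports no observed attrition and states no alpha, and nothing in it says that dropouts' diary days will be discarded.

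**Conclusion.** The statement is wrong as written. The target of 139 comes from multiplying by 1.30, and covering 30% attrition from a base of 107 needs 153. The tolerances are about 23% for 139 and about 25.7% for the 144 enrolled. These figures, and the roughly 97 and 101 participants left at 30%, rest only on the article's own inputs and on counting participants as it does.

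The consequence is modest. Under the assumptions in step 5, the worst-case loss of power is about 4 percentage points for 139 and about 2 to 2.5 points for 144. Those power figures are approximate and conditional, and partial diary data could remove the loss altogether. This is a correction to a stated figure. It does not show that the study is underpowered, and it touches no outcome, model or analysis.

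**What to change.** Recruitment is closed, so restate what the numbers cover and leave the target as the historical figure. For example:

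> The recruitment target was 139, which retains about 107 participants for attrition up to about 23%. The 144 students enrolled retain about 107 for attrition up to about 25.7%; at 30% attrition about 101 would remain.

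Remove the claim that 139 covers 30%. If a power figure at 30% attrition is added (about 76% for 139, about 78% for 144), label it as approximate and state its basis: an assumed alpha of 0.05, square-root-of-N scaling from 80% at 107, and no diary data from dropouts. Add that partial diary data would reduce or remove the shortfall.

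The cost is one rewritten sentence and a slightly less favourable attrition tolerance. No analysis has to change.

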### Baseline Cohort Characteristics

A total of 144 students were enrolled in the study and completed baseline assessments. Baseline characteristics are presented in Table 2. Participants were approximately 18 years of age and slightly more likely to identify as female (54.9%) than male. The sample was predominantly White (78.5%), with 16.7% identifying as first-generation college students. Students were enrolled across multiple academic colleges within the university, most commonly Health and Human Sciences (29.9%), Engineering (27.8%), and Arts and Sciences (20.8%). At baseline, 80.6% of participants reported no prior mental health diagnosis, 16.0% reported a current diagnosis, and 2.1% reported a previous diagnosis that was not current. All participants provided informed consent prior to participation. The study protocol was approved by the Kansas State University Institutional Review Board (IRB #12780).

### Measures

#### Depressive Symptoms (Primary Outcome).

Depressive symptoms were assessed using both panel and intensive daily diary measures. At baseline and monthly panel assessments (Weeks 0, 4, 8, 12, and 16), symptoms were measured using the 8-item Patient Health Questionnaire (PHQ-8),^56^ a widely validated instrument with strong psychometric properties in college and emerging adult populations.^57,58^ The PHQ-8 excludes the suicidality item from the original PHQ-9,^59^ an approach commonly used in large-scale epidemiologic and community-based research. The suicidality item was excluded to align with the study’s safety monitoring protocol for periodic, self-administered assessments without real-time clinical follow-up. Prior studies indicate that omission of the suicidality item has minimal impact on overall depression severity scoring, as this item is the least frequently endorsed in general population samples and contributes little to total score variance.^59–62^ Items assess symptom frequency over the prior two weeks and are rated on a 4-point scale from 0 (“Not at all”) to 3 (“Nearly every day”), with higher scores indicating greater depressive symptom severity.

During each 7-day burst period, participants completed a daily diary adaptation of the PHQ-8 assessing symptoms experienced since waking that day.^63^ Item selection and wording were informed by an established experience sampling repository (i.e., the ESM Item Repository) to ensure ecological validity and alignment with intensive longitudinal measurement practices.^64^ Items are presented in Supplementary Materials Table 1. The suicidality item was excluded due to safety monitoring constraints in unsupervised daily assessment contexts. To enhance conceptual specificity for network modeling, selected items were decomposed into theoretically distinct components. Specifically, the psychomotor agitation/retardation item was separated into two items distinguishing slowed movement/speech from restlessness, and the sleep item was divided to differentiate difficulty initiating or maintaining sleep (“trouble falling asleep or staying asleep”) from hypersomnia-related symptoms (“slept more than usual”). As a result of these modifications, the daily diary instrument included 10 depressive symptom items. Daily items were rated on a five-point scale ranging from 0 (“Not at all”) to 4 (“Very much”) and were administered at 8:00 pm, with automated hourly reminders at 9:00 pm and 10:00 pm before the survey closed at 11:00 pm. To support participant well-being, information about free university psychological services was provided upon completion of each daily diary.

#### Anxiety Symptoms (Secondary Outcome).

Anxiety symptoms were assessed given the high comorbidity and substantial symptom overlap between anxiety and depressive disorders,^65^ including evidence of interconnected symptom networks.^40,66^ Anxiety frequently co-occurs with depression during emerging adulthood,^67^ and symptom overlap may influence network dynamics and temporal associations with 24-hour movement behaviors. At baseline and monthly panel assessments, anxiety was measured using the 7-item Generalized Anxiety Disorder scale (GAD-7), a widely validated instrument with strong psychometric properties in college and emerging adult populations.^68^ Items assess symptom frequency over the prior two weeks using a 4-point scale from 0 (“Not at all”) to 3 (“Nearly every day”).

During each intensive burst period, anxiety symptoms were assessed daily using a 6-item adaptation of the GAD-7 referencing symptoms experienced since waking that day.^63^ Items are presented in Supplementary Materials Table 1. The item “Feeling so restless that it was hard to sit still” was excluded due to substantial conceptual overlap with the PHQ-8 psychomotor agitation item, thereby reducing redundancy across daily symptom measures and minimizing participant burden. Daily items were rated on a five-point scale from 0 (“Not at all”) to 4 (“Very much”).

#### 24-Hour Movement Behaviors (Primary Exposure).

Daily 24-hour movement behaviors were assessed using a wrist-worn Fitbit Charge 6 device provided at baseline and worn continuously (24 hours/day) throughout the 108-day study period. The device uses triaxial accelerometry and photoplethysmography-derived heart rate data to estimate time spent in sleep, SB, LPA, moderate PA (MPA), and vigorous PA (VPA) using proprietary algorithms. Daily aggregated time-based estimates for each intensity category were obtained via secure synchronization through the Fitbit mobile application and the Pathverse research platform. Daily time in sleep, SB, LPA, MPA and VPA will be used to derive 24-hour time-use compositions, with MPA and VPA combined into a single MVPA category for analysis.

Primary validation studies of Fitbit Charge and other wrist-worn Fitbit models demonstrate strong agreement with polysomnography for estimating total sleep time in young adults,^69,70^ and acceptable agreement with research-grade accelerometers for estimating time spent in intensity-based activity categories under free-living conditions.^71–80^ Although Fitbit devices rely on proprietary classification algorithms that likely reflect individualized (relative) rather than fixed absolute intensity thresholds,^81^ the present study emphasizes within-person day-to-day variation in 24-hour time-use distributions rather than absolute energy expenditure. Accordingly, minor classification error at specific intensity thresholds is unlikely to meaningfully bias inferences. Given the study’s focus on continuous day-to-day monitoring across a 108-day period, the Fitbit Charge 6 was selected as a practical, low-burden device capable of supporting continuous free-living assessment in emerging adults.

#### Daily Contextual Covariates (Burst Assessments).

During each burst period, participants completed additional daily items assessing contextual and affective factors experienced since waking that day. These items included: 1) Perceived stress; 2) Happiness; 3) Sleep quality (previous night); 4) Academic demands; and 5) Injury or illness status. Items were rated on a five-point scale from 0 (“Not at all”) to 4 (“Very much”), with the exception of sleep quality, which was scored from 0 (“Very poor”) to 4 (“Very good”). These variables were included as time-varying contextual covariates to account for daily influences on 24-hour movement behaviors and depressive symptoms. Items are presented in Supplementary Materials Table 1.

#### Daily Contextual Covariates (Weather).

Daily weather data, including high and low temperature, precipitation, humidity, and wind speed (average and max), were obtained retrospectively from the Kansas Mesonet station most proximal to campus (North Agronomy Farm) and linked to participant-level data by calendar date. These variables were assessed as time-varying environmental covariates.

#### Daily Contextual Covariates (Campus Recreation Center Usage).

Daily campus recreation center access data were obtained from university administrative records. Participants provided their student identification numbers at baseline, which were used to link recreation center entry records (via facility swipe access) to participant-level data by calendar date. Records reflected whether participants accessed campus recreational facilities on a given day. Facility usage was included as a time-varying covariate.

#### Monthly Psychosocial and Behavioral Measures.

At baseline and monthly panel assessments, participants completed validated measures assessing psychosocial, behavioral, and contextual factors relevant to mental health and PA. These included measures of loneliness,^82^ perceived stress,^83^ sleep quality,^84^ social support,^85^ college adjustment,^86^ stressful life events,^87^ body-related attitudes and behaviors,^88^ time spent in nature, and PA motivational constructs.^89–91^ A summary of panel measures, instruments, and assessment timing is provided in Table 3. A mid-study check-in survey at Week 8 assessed participant satisfaction, perceived barriers, technical issues, and suggestions for study improvement.

#### Baseline Demographic and Health Measures.

At baseline, participants reported demographic characteristics including age, sex, race/ethnicity, college of enrollment within the university, first-generation college status, parental education (proxy for socioeconomic status), residence hall, self-rated health, food security, and home ZIP code. Home ZIP codes were used to classify participants’ rural-urban residence status using established 2020 Rural-Urban Commuting Area (RUCA) codes.^92^

Height, weight, waist circumference, and hip circumference were measured during the laboratory visit. Height and weight were measured using a calibrated Health O Meter Professional 349KLX digital floor scale and stadiometer. Waist circumference was measured using a measuring tape placed midway between the lowest rib and the iliac crest while the participant was standing. Hip circumference was measured using a measuring tape placed at the level of the maximum circumference over the buttocks while the participant was standing with feet together and weight evenly distributed. Body mass index (BMI) was calculated as weight (kg)/height (m ). Waist-to-hip ratio (WHR) and waist-to-height ratio were computed to characterize central adiposity and abdominal fat distribution. Participants were classified as having abdominal obesity if their waist-toheight ratio was ≥ 0.50, consistent with established clinical cutpoints.^93^

Participants also reported current and past mental health diagnoses, psychiatric medication use, chronotype (i.e., individual differences in circadian preference for morning versus evening activity and alertness; Morningness–Eveningness Questionnaire),^94^ PA participation (Exercise Vital Sign),^95^ and resilience (Brief Resilience Scale).^96^ Participants provided personalized academic schedules (daily class hours), which were used to calculate instructional hours per day and identify the timing of key academic assessments (e.g., exams, major assignments). These data were incorporated into the daily time-series dataset to account for academic time demands and assessment timing.

#### Additional Health Measures (Follow-Up Assessment).

A follow-up health assessment visit which took place in the last three weeks of the study was added to the study protocol via amendment during the data collection period. At this visit, anthropometric measures (height, weight, waist circumference, and hip circumference) were repeated. Additional assessments introduced at follow-up included body composition, maximal handgrip strength, and resting blood pressure.

Body composition was assessed via bioelectrical impedance analysis using a Tanita DC-430U Multi-Frequency Total Body Composition Analyzer. Participants were instructed to empty their bladder prior to assessment. Maximal handgrip strength was measured using a Jamar Plus+ Digital Hand Dynamometer; participants completed three trials with their dominant hand, and the highest value was retained for analysis. Resting blood pressure was measured using an automated Omron Digital Blood Pressure Monitor (HEM-907XL) after participants rested quietly for two minutes. The average of two readings was recorded; a third measurement was obtained if the first two differed by ≥ 10 mmHg.

### Study Protocol

Eligible participants attended a baseline laboratory visit between August 25 and September 5, 2025. During this visit, trained research staff obtained anthropometric measurements, and participants completed baseline survey assessments. Participants were then provided with a Fitbit Charge 6 device, which was placed on their non-dominant wrist. Study staff assisted participants in downloading the Fitbit and Pathverse applications to their smartphones and guided them through secure linking and synchronization to enable data sharing with the research team. Participants were also randomized to one of six pre-specified intensive burst sequences (see Study Design) via study identification-level allocation. Specifically, study identification numbers were randomly assigned to the six sequences prior to enrollment, and participants were subsequently assigned to study identification numbers based on their selected scheduling timeslot.

Panel surveys were administered every four weeks following baseline via email and the Pathverse application. Participants were given five days to complete each panel survey. Each survey required approximately 20 minutes to complete and included three attention-check items to promote data quality. The intensive burst protocol commenced on September 2, 2025. Participants who enrolled after this date were randomized to their assigned burst sequence at baseline; for those assigned to Block S1 or S2 whose scheduled burst days occurred prior to enrollment, those days were not assessed and were coded as missing. During each 7-day burst period, daily surveys were delivered via the Pathverse application, with item order randomized at each administration. Surveys were released at 8:00 PM and remained accessible until 11:00 PM. Automated push notifications were sent at 8:00 PM, with reminder notifications at 9:00 PM and 10:00 PM if the survey remained incomplete.

Following the university’s fall break, participants were invited to return to the laboratory for a follow-up health assessment visit between December 1 and December 19, 2025. Repeat anthropometric measurements were obtained, and additional assessments included body composition via bioelectrical impedance analysis, maximal handgrip strength, and resting blood pressure (see Measures section for detailed procedures). Following study completion on December 19, 2025, participant engagement was reviewed, and compensation was calculated according to the pre-specified incentive plan. Digital gift cards were subsequently distributed via email.

